### Randomization

All eligible participants who consent to participate in the study and complete the baseline data collection will be randomized to either SSC or LT-NRT. Randomization will be determined by computer-generated random numbers and a randomization module embedded in the data capture program.

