## Measures

**Outcome measures.** Our selection of outcomes was derived from scientific expert consensus and informed by input from our stakeholders and smokers with COPD. (Table 4) The primary outcome is biochemically verified 7-day point prevalence smoking abstinence defined as no cigarettes (not even a puff) for the previous 7 days at month 12. Biochemical validation will be based on expired CO, consistent with consensus statements from the Society for Research on Nicotine and Tobacco (SRNT). For those participants who have reported they have quit smoking and who are unable to be verified in this way, we will obtain verbal permission and contact information for a household member or other regular contact to provide proxy validation.

Secondary outcomes are 6 month sustained abstinence (biochemically verified), number of quit attempts, average CPD over the year of the study, and cumulative exposure to CO and NNAL. We will examine relapse rates 3 months after the conclusion of the study for participants who report they have quit smoking at the 12-month assessment. Clinical outcomes include both objective and subjective measures of respiratory function based on the measured FEV1 (as a percent of predicted) and the COPD Assessment Test.

We will also track both respiratory and cardiac clinical events. This will be done by self-report of intercurrent emergency department visits and hospitalizations at each follow-up visit. We will validate both the occurrence and the nature of these self-reported clinical events by blinded physician review of medical records.

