| Respiratory function                               | Simple spirometry will be performed at baseline and at the final follow-up visit. (baseline, Mo12)                                                                                                                                                                   |
| Respiratory symptoms                               | Respiratory symptoms will be measured using the COPD Assessment Test (baseline, Mo 3, 6 & 12)                                                                                                                                                                        |
| Respiratory-related hospitalizations and ED visits | Intercurrent hospitalizations and emergency department visits will be assessed at each follow-up visit. Patients will be asked to classify the event as related to their heart or breathing. These will be validated by blinded physician review of medical records. |
| Cardiac-related hospitalizations and ED visits     |                                                                                                                                                                                                                                                                      |

\*Primary outcome

self-report of CPD or they looked at nicotine metabolites (i.e. cotinine). Self-report of CPD is highly problematic, because even if smokers really do reduce the number of cigarettes they smoker, they tend to smoke those cigarettes more efficiently, and cotinine measurements are confounded by the use of therapeutic NRT. Our measures of CO and NNAL will allow us to have objective measure of actual smoke exposure. The NNAL is particularly relevant to our patients who would like to reduce exposure to carcinogens. NNAL (4-(methylnitrosamino)-1-(3)pyridyl-1-butanol) is a pulmonary carcinogen and metabolite of 4-(methylnitrosamino)-1-(3)pyridyl-1-butanone (NNK), a tobacco-specific nitrosamine related to the development of lung cancer. NNAL assessed in urine is highly correlated with smoke-related tobacco exposure.

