### Covariates

We will collect a variety of covariates (Table 5). These covariates will allow us to verify the comparability of the two comparison arms at baseline and will also allow us to estimate treatment effects for given personal characteristics (see discussion of CART analysis in the analytic plan). We will assess demographic variables, social history variables that might influence tobacco consumption, smoking related variables, including cpd, nicotine dependence, and biological markers of nicotine consumption, and clinical variables including both objective and subjective assessment of respiratory function and prior history of respiratory-related clinical events.

| Table 5. Co-variate measures |                                                                                                                                                                                  |
|------------------------------|----------------------------------------------------------------------------------------------------------------------------------------------------------------------------------|
| Construct                    | Measure (assessment timepoint)                                                                                                                                                   |
| Demographics                 | gender, age, race, ethnicity, income, education, employment, marital status, family structure (baseline)                                                                         |
| Social history               | Other smokers in the home, presence of home smoking restrictions, anxiety (GAD-2), depression (PHQ-2), health history (baseline)                                                 |
| Smoking Variables            |                                                                                                                                                                                  |
| Smoking history              | Quantity smoked (baseline, Mo 3, 6 & 12), quitting history, use of other tobacco and nicotine products, including e-cigs and NRT, (baseline)                                     |
| Readiness to quit            | Interest in quitting will be assessed using 30 day anchor (stage of change) and 12 months (intent to cut back or quit) (baseline, Mo 3, 6 and 12)                                |

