| Nicotine dependence          | Fagerström Test for Nicotine Dependence (FTND) ,  time to first cigarette (baseline, Mo 12); Brief WISDM  among continued smokers at month 12. |
| Nicotine intake              | Urinary cotinine/creatinine ratio (baseline, Mo 3, 6, and 12)                                                                                                                    |
| Clinical Variables           |                                                                                                                                                                                  |
| Respiratory function         | FEV1 (baseline)                                                                                                                                                                  |
| COPD symptoms                | CAT score, # of hospitalizations for COPD in past year (baseline)                                                                                                                |
| Treatment Variables          |                                                                                                                                                                                  |
| Medication adherence         | 3-day medication use recall (Mo 3, 6, and 12)                                                                                                                                    |
| Counseling adherence         | total counseling sessions completed                                                                                                                                              |

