### Analytical Plan.

**Sample Size and Power Calculations.** Our sample size was based on our primary outcome, point-prevalence abstinence at Month 12, using an intent-to-treat approach. Based on prior studies using precessation NRT, we estimate a 2-fold increase in cessation outcomes in the LT-NRT group compared to the SSC group. Given our recruitment of patients at all levels of readiness to quit, we estimate a 12 month cessation rate of 10%. With 199 participants, in each arm, we will have an 80% power to detect a 2-fold difference or greater with a Type I error rate of 5%. This sample size will provide comparable power for looking at 6 month sustained cessation. For the CO measured longitudinally at four time points, we have 80% power to detect a mean difference of 2.24 ppm. Likewise, for NNAL, we have 80% power to detect a mean difference of 0.41 pmol/mg creatinine or more between the two groups.

**Specific Aim 1: Compare the benefits of traditional smoking cessation (SSC) versus long-term guided maintenance therapy (LT-NRT) with NRT.** The chi-square test will be used to compare the verified 7-day point prevalence abstinence at Month 12 between the two groups. If there is imbalance between treatment groups at baseline, we will switch to logistic regression for our primary analysis. We will use similar methods to test for group differences for dichotomous secondary outcomes including sustained abstinence and proportion with 1 or more ED visits or hospitalizations. To test for differences in change in respiratory symptoms and FEV1 from baseline measured at 3, 6, and 12 months, we will use standard mixed models repeated measures analysis. Likewise, to test for differences in longitudinal exposure to CO and NNAL, we will compare the area under the curve over the entire 12 months of follow-up using repeated measures analysis. If the treatment differences are heterogeneous across any covariate sub-groups, we will quantify and report such interactions

with appropriate contrast statements. We will compare the cumulative number of self-reported quit attempts by means of a Wilcoxon rank-sum test.

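### The protocol specifies the CAT comparison as change from baseline and names no baseline term, which as written gives up some precision that a baseline score already collected could supply

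*Protocol*

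**What the plan says.** In the protocol's Analytical Plan, under Specific Aim 1, the plan for this outcome is: "To test for differences in change in respiratory symptoms and FEV1 from baseline measured at 3, 6, and 12 months, we will use standard mixed". The analysis named there is one for repeated measures. No fixed effects, covariates or covariance structure are listed.

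The other relevant places in the protocol are:

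- **Measures, clinical outcomes:** "Clinical outcomes include both objective and subjective measures of respiratory function based on the measured FEV1 (as a percent of predicted) and the COPD Assessment". CAT is therefore a named clinical outcome, though not the primary one.
- **Measures, Table 4:** "Respiratory symptoms will be measured using the COPD Assessment Test (baseline, Mo 3, 6 & 12").
- **Covariates, Table 5:** baseline CAT appears again as a covariate measure: "CAT score, # of hospitalizations for COPD in past year (baseline").
- **Randomization:** "All eligible participants who consent to participate in the study and complete the baseline data collection will be randomized to either SSC or LT-NRT". Baseline CAT should therefore exist for essentially everyone randomized.
- **Covariates, stated purpose:** "These covariates will allow us to verify the comparability of the two comparison arms at baseline". The second stated purpose is to estimate treatment effects for given patient characteristics.
- **Analytical Plan, rule on imbalance:** "If there is imbalance between treatment groups at baseline, we will switch to logistic regression for our primary analysis". Similar methods are then extended to dichotomous secondary outcomes. CAT is not dichotomous, so this rule does not reach it.

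**The concern.** A change score subtracts the whole baseline value, which fixes the slope of follow-up on baseline at 1. When the SDs at the two times are equal, the actual slope is rho, which is below 1 for a symptom score. The change score then over-corrects: it removes the part of baseline that predicts follow-up and adds back some baseline noise.

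The usual ways of carrying out the sentence as written lead to the same estimate:

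- If change is the response and no baseline term is added, the comparison is the difference in mean change.
- If all four CAT measurements are responses with an unconstrained group-by-visit effect, the contrast for change at a visit is, with complete data, again the difference in mean change.

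Precision is recovered only by a baseline covariate or by constraining the arms to a common baseline mean. The protocol states neither.

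What is at stake is power on a patient-reported outcome for which the trial was not sized. The protocol's Measures section argues that a COPD population gives a better chance of seeing differences in clinical outcomes.

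**Working it through.** **1. The plan's own figure.** The protocol says: "With 199 participants, in each arm, we will have an 80% power to detect a 2-fold difference or greater with a Type I error rate" (the rate given is 5%). The assumed rates are 10% and, with a 2-fold increase, 20%. For a two-sided test with pooled variance and no continuity correction:

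n = [1.96·√(2·0.15·0.85) + 0.8416·√(0.10·0.90 + 0.20·0.80)]² / 0.10² = (0.990 + 0.421)² / 0.01 ≈ 199 per arm.

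The figure reproduces (power 80.0% at 199 per arm). It concerns abstinence only. No SD, effect size, correlation or power is stated for CAT, so there is no CAT figure to reproduce.

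**2. Variances for CAT at month 12.** Units are the CAT variance, taken as equal at baseline and follow-up (an assumption).

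- Change score: 2(1 − rho)
- Baseline-adjusted: 1 − rho²
- Ratio, adjusted to change: (1 − rho²) / [2(1 − rho)] = (1 + rho)/2

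The ratio is below 1 for every rho below 1.

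**3. Power.** Take an effect that the change score detects with 80% power (two-sided 5%). The power with adjustment is Φ[(1.96 + 0.8416)/√ratio − 1.96]. At rho 0.5 this is Φ(2.8016/0.866 − 1.96) = Φ(1.275) = 0.899. The last column reverses the anchor: the power of the change score for an effect that the adjusted analysis detects with 80%.

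| Assumed rho | Variance ratio | Adjusted power when change has 80% | Change power when adjusted has 80% |
|---|---|---|---|
| 0.5 | 0.75 | 89.9% | 67.9% |
| 0.6 | 0.80 | 87.9% | 70.7% |
| 0.7 | 0.85 | 86.0% | 73.3% |
| 0.8 | 0.90 | 84.0% | 75.7% |
| 0.9 | 0.95 | 82.0% | 78.0% |

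**4. Detectable difference, 199 analysed per arm.** The formula is 2.8016·√(variance·2/199). At rho 0.5 the change score gives 2.8016·√(1.00·2/199) = 0.281 SD and the adjusted analysis gives 2.8016·√(0.75·2/199) = 0.243 SD. At rho 0.8 the values are 0.178 and 0.169 SD.

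**5. Chance baseline imbalance.** The change-score estimate shifts by −(1 − rho) for each unit of chance baseline difference between arms. The excess variance is 2(1 − rho) − (1 − rho²) = (1 − rho)², which is exactly the variance that this shift contributes. The two are therefore one loss. With 199 per arm the SD of the baseline difference is √(2/199) = 0.100, so a one-SD imbalance moves the estimate by 0.05 SD at rho 0.5 and 0.02 SD at rho 0.8.

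**6. Check by simulation.** With rho 0.6, 199 per arm and 4,000 replicates, the variance ratio was 0.80. The slope of the estimate on the baseline difference was −0.40 unadjusted and 0.00 adjusted. Both agree with the formulas.

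**The case against.** The strongest reply is that the protocol never says baseline is left out. It names a model class and a quantity to be tested, and lists no terms at all. Fixed effects for a non-primary outcome are commonly settled in the SAP, and the sentence is compatible with a model that includes baseline CAT. This stands. A reader might infer that the trial has chosen an unadjusted change analysis, but the text supports only that change is specified and no baseline term is named.

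A reader might also infer from the Covariates section that adjustment is ruled out, because only two uses are given. That does not follow. The section says what the covariates will allow, not what they are limited to. Table 5 lists baseline CAT among the covariates, and the imbalance rule shows that adjustment is contemplated elsewhere.

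A third tempting reading is that the analysis is biased, or that imbalance is a further harm on top of lost precision. Neither holds. Across randomizations the unadjusted change score is unbiased, and step 5 shows that the imbalance effect is the precision loss seen from another side.

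The size is also open to challenge. No rho is given, 80% is only an anchor, and the gain shrinks to 4 points at rho 0.8 and 2 points at 0.9. The protocol expects missing data, so 199 analysed per arm is optimistic for the detectable differences. The power conversion in step 3 does not itself contain n.

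What survives is narrower. The sentence fixes change as the quantity to be tested, and carried out as it stands it gives the less precise contrast. A better method is available from data already collected.

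**Conclusion.** The point holds as a minor, cost-free improvement to a non-primary analysis. The protocol specifies CAT as change from baseline in a repeated-measures mixed model without naming a baseline term. If nothing is added, the comparison is valid but less efficient than it could be.

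Over an assumed rho of 0.5 to 0.9, the variance with adjustment is 75% to 95% of the change-score variance, and 80% power at month 12 becomes about 90% down to 82%. This rests on equal variances at baseline and follow-up, both analyses using the same participants, and an anchor of 80% power that the protocol does not state for CAT.

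FEV1 shares the sentence but would gain little: if its rho is near 0.9 (also an assumption), the gain is about 2 points.

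**What to change.** Replace the respiratory-symptom part of the sentence under Specific Aim 1 with wording such as: *CAT score at months 3, 6 and 12 will be analysed by a mixed model for repeated measures with treatment, visit, treatment-by-visit, baseline CAT and baseline-by-visit as fixed effects; the adjusted difference between arms at month 12 will be reported.* With baseline and its interaction with visit in the model, it makes no difference to the estimate whether CAT or its change is the response.

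If the SAP already specifies this, only the protocol sentence needs aligning. The cost is a few degrees of freedom (one for baseline CAT and two for its interaction with three visits) in a trial of 398. No new data, visits or participants are needed.

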#### *Sources of Materials*

This study involves testing alternative methods for reducing the harms of smoking and supporting smoking cessation among smokers with COPD. We will provide participants with standardized information on smoking cessation and the appropriate use of NRT. We will gather data from all of our study participants at baseline and months 3, 6, and 12. Information gathered will include surveys, medical records information, measures of respiratory function, urinary measures of nicotine and cigarette smoke exposure, and measures of expired carbon monoxide (to measure smoke exposure). The baseline questionnaire will collect information related to demographics, smoking history, and health status questions. At baseline, 3, 6, and 12 months, we will collect urine specimens, exhaled CO and will administer a brief survey assessing their current smoking, respiratory symptoms, and history of COPD-related hospitalizations or emergency room visits. In addition, at baseline and Month 12, we will collect a measure of their breathing (i.e., spirometry).

All questionnaires and informed consent documents will be submitted to the KUMC IRB for approval prior to implementation.

The KUMC Department of Preventive Medicine and Public Health has a well-developed structure for data management. Working data is maintained on a single large file server. Inactive files are moved to archival storage under control of an automated system, itself controlled by a DBMS (Ingres) based request system that ensures that all data movement is appropriately logged and commented. The archival storage is hosted on the institutional mainframe computer, which also supports billing and registration. The use of the mainframe ensures several high level support functions for the archive system (e.g., storage in separate fire zones, regular copying of data to new media, and guaranteed availability).

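### The analysis text takes FEV1 change at 3, 6 and 12 months into a repeated-measures model, but spirometry is scheduled only at baseline and month 12, so the model reduces to one month-12 comparison

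*Protocol*

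**What the plan says.** The Analytical Plan, under Specific Aim 1, treats respiratory symptoms and FEV1 together: "To test for differences in change in respiratory symptoms and FEV1 from baseline measured at 3, 6, and 12 months", it states, "we will use standard mixed models repeated measures analysis".

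The measurement schedule separates the two outcomes:

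- **FEV1, Table 4 (Measures):** "Simple spirometry will be performed at baseline and at the final follow-up visit. (baseline, Mo12".
- **FEV1, Sources of Materials:** "at baseline and Month 12, we will collect a measure of their breathing (i.e., spirometry". The preceding sentence lists what is gathered at every visit, starting "At baseline, 3, 6, and 12 months, we will collect urine specimens, exhaled CO and will administer a brief survey", and spirometry is not in that list.
- **Symptoms, Table 4:** "Respiratory symptoms will be measured using the COPD Assessment Test (baseline, Mo 3, 6 & 12".

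The Measures section describes the clinical outcomes as "objective and subjective measures of respiratory function based on the measured FEV1 (as a percent of predicted", together with the CAT. Table 5 also lists "FEV1 (baseline" among the covariates, so a baseline value is already being collected.

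**The concern.** The protocol does not leave the FEV1 analysis open. It names both a model and the visits that feed it, and two of the three visits produce no FEV1 data under the protocol's own schedule. An analyst who follows the sentence literally has nothing to enter for months 3 and 6 and must choose a replacement, such as a change score, ANCOVA or a two-occasion mixed model. These differ in precision and in how they treat people without a month-12 value. If the choice is not fixed beforehand, it may be made with the data in view. What is at stake is the pre-specification, and possibly some precision, of a secondary clinical outcome that patients and stakeholders asked for.

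**Working it through.** **1. Schedule against analysis text**

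| Outcome | Visits named in the analysis | Visits at which it is measured | Post-baseline values |
|---|---|---|---|
| CAT | 3, 6, 12 | baseline, 3, 6, 12 | 3 of 3 |
| FEV1 | 3, 6, 12 | baseline, 12 | 1 of 3 |

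The Study design and Study visits sections speak generally of assessments at 3, 6 and 12 months. Neither names spirometry. The two places that do name it agree with each other.

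**2. How much FEV1 data the stated model would have.** With 199 per arm there are 2 × 199 = 398 participants. Three follow-up visits would give 398 × 3 = 1,194 change values. The schedule gives at most 398, before any dropout.

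**3. What can be estimated.** A model of change by arm, visit and arm-by-visit at 3, 6 and 12 months has 6 fixed-effect columns: intercept, arm, two visit indicators and two interactions. With FEV1 present only at month 12, the month-6 columns are all zero, the month-12 indicator equals the intercept, and its interaction equals the arm column. A numerical check gave rank 2. Only the month-12 mean and the month-12 arm difference remain. Effects at months 3 and 6, and the within-person covariance of changes, cannot be estimated.

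**4. What remains.** A mixed model on the two raw occasions (baseline and month 12, with an arm-by-time term) was fitted to one simulated data set of 398 participants with no missing values. It gave an arm difference of 0.012 with standard error 0.630. A two-sample comparison of change gave the same estimate and standard error. So FEV1 is analysable, and with complete data and unconstrained baseline means the mixed model is the change-score comparison.

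**5. Possible precision difference.** Let s² be the FEV1 variance, assumed equal at baseline and month 12, and rho the correlation between the two. The protocol gives no value for rho, so 0.7 to 0.9 is an assumed range.

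- Variance of raw change: 2s²(1 − rho)
- Residual variance after adjusting month 12 for baseline: s²(1 − rho²)
- Ratio: (1 − rho²) / [2(1 − rho)] = (1 + rho)/2

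| rho (assumed) | (1 + rho)/2 | Variance reduction | Standard-error reduction, 1 − √ratio |
|---|---|---|---|
| 0.7 | 0.85 | 15% | 7.8% |
| 0.8 | 0.90 | 10% | 5.1% |
| 0.9 | 0.95 | 5% | 2.5% |

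**6. The protocol's own sample size.** No power statement is made for FEV1. For the primary outcome, 10% against 20% with a two-sided 5% test (sidedness is not stated; two-sided reproduces the figure), pooled variance and no continuity correction gives 199 per arm and power 0.800. The stated figure reproduces and does not depend on FEV1.

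**The case against.** The best defence is that this is loose drafting. Two outcomes share a sentence, the schedule is stated twice and consistently, and a competent analyst would see that FEV1 has one follow-up value. Most of that stands, and it is why the point is a small one. It does not remove the mismatch, because the text still prescribes an analysis of values that are never collected.

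Four stronger readings are tempting and are not supported:

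- **That the FEV1 analysis cannot be run at all.** A two-occasion mixed model can be fitted. Only the month 3 and 6 effects are out of reach.
- **That it becomes an unadjusted, complete-case comparison.** The protocol does not say whether baseline enters as a covariate or as a response. As a covariate, the single-visit model is already ANCOVA. As a response, a likelihood model keeps participants who have only a baseline value. Such detail is commonly left to a statistical analysis plan, which is not shown here.
- **That 5 to 15% of variance is definitely being lost.** The arithmetic is right, but it applies only if raw change without baseline adjustment was intended, and the correlations are assumed.
- **That FEV1 is the only objective clinical outcome.** Hospitalizations and emergency visits are also clinical outcomes in Table 4, validated by blinded review of medical records. FEV1 is the objective measure of respiratory function.

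**Conclusion.** The contradiction holds and needs no assumption: the analysis sentence calls for three post-baseline FEV1 values where the schedule provides one. The stated model reduces to a month-12 comparison. Any effect on precision is conditional, rests on equal variances and the assumed range of rho, and is nil if baseline was already to be a covariate.

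The reach is limited to one secondary clinical outcome. A reader might infer that the trial's main conclusion is at risk. It is not, since the primary test of verified abstinence at month 12 and its sample size do not involve FEV1. The text should be corrected, but this is not an error that must be fixed before the trial can be relied on.

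**What to change.** Revise the sentence in Specific Aim 1 so that it agrees with Table 4 and Sources of Materials:

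1. Limit the mixed repeated-measures analysis of change at 3, 6 and 12 months to the CAT.
2. State that FEV1 (percent predicted) is compared between arms at month 12 by ANCOVA with baseline FEV1 as covariate, or by an equivalent two-occasion likelihood model of baseline and month 12 with a common baseline mean.

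The common baseline mean matters: with separate baseline means, the two-occasion model returns the raw change comparison on complete data. How missing month-12 FEV1 is handled can be left to the statistical analysis plan.

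The cost is two sentences. It needs no added visit, spirometry or participant, because baseline FEV1 is already collected.
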